### 2.20. Frequency and procedures for auditing trial conduct

The Investigator shall allow direct access to trial data and documents for monitoring, audits and/or inspections by competent regulatory or health authorities. As such, e-CRFs, source records and other trial-related documentation must be kept current, complete, and accurate at all times.

### 2.21. Ethics approval and consent to participate

The study protocol version 3.0 (February 10th, 2020), EudraCT number 2019-004498-18, received local IRB approval (Ethics and Clinical Investigation Committee of the Bellvitge University Hospital, code AC049/19) on February 27th, 2020). Notably, due to the COVID-19 pandemic and the difficulty obtaining the study medication (EFV), the start of this clinical trial was halted for 2 years. After this period, the protocol was updated to version 3.1 (March 24th, 2020). The local IRB approved this new version on April 15th, 2022. The list of local IRB members is available at https://bellvitgehospital.cat/es/investiga-con-nosotros/ceic/composicion. Accessed on August 1st, 2022.

This Trial will be conducted according to the criteria set by the Declaration of Helsinki (revised on WMA 64th General Assembly, Fortaleza, Brazil, October 2013), good clinical practice standards and applicable regulations. A specific insurance will be hired for this clinical trial.

The level of confidentiality protection, in terms of personal data protection, as required by Spanish (Organic Law on Data Protection 3/2018) and European Law (Regulation EU 2016/679 of the European Parliament and Council), was also ensured (see item 2.25).

Every patient that accepts to participate in the study will be assigned consecutive numbers as they are enrolled, and these numbers (or codes) will be used in the eCRF, instead of personal data. The data collected will be encoded, so that the patient to whom they correspond is not identified.

### 2.22. Plans for communicating important protocol amendments to relevant parties

Major protocol changes will be submitted for IRB approval and minor outcomes will be informed to the IRB. As per good clinical practice, trial participants will be informed of any significant changes during the trial.

### 2.23. Who will obtain informed consent?

The PI (or another physician from the study team) will inform the screened patients about the study and ask them to sign the written informed consent in visit 1 if the patient is interested in participating in the study.

### 2.24. Additional consent provisions for collection and use of participant data and biological specimens

As mentioned before, an optional lumbar puncture will be performed to determine CSF biomarkers (i.e., Beta-amyloid, Tau, and phosphorylated Tau) in those patients who agree to undergo this procedure. An additional written informed consent is required prior to performing the lumbar puncture. Samples will be stored and patients will be informed about the storage along with all study procedures by the recruiting investigator (see item 3.3).

### 2.25. Confidentiality

The results from this clinical trial are confidential and may not be transferred to third parties in any form or manner without written permission from the Sponsor. All individuals involved in the clinical trial are bound to this confidentiality clause in line with the Regulation (EU) 2016/679 of the European Parliament and of the Council of April 27th, 2016, on the protection of natural persons concerning the processing of personal data and the free movement of such data, as well as all other valid and applicable laws and regulations, such as the “Organic Law 3/2018 on Personal Data Protection and Digital Rights Assurance. Therefore, patient data will be anonymized.

While obtaining a signature for the Written Informed Consent, the investigator will request written permission from the patient to directly access his/her data. With this permission granted, the patient’s data may be examined, analyzed, verified, and reproduced for the clinical trial evaluation.

Data will be anonymized so that the corresponding patient cannot be identified. Patient data will also be dissociated. Patients will be assigned consecutive numbers as they are enrolled in the study, and these identification numbers (or codes) will be used in the e-CRF; the patient’s full name will not be included in the e-CRFs. The principal investigator of each center will keep an updated patient identification list containing the name, clinical history number, and the patient’s identification number (or code) for the clinical trial.

The study monitor may have access to the patient’s identity and data related to the study monitoring procedures. Any person with direct access to the data (Regulatory Authorities, Trial Monitors, and auditors) will take all possible precautions to maintain the confidentiality of patients’ identities.

It is the investigator’s responsibility to obtain written informed consent from the study patients. It is the Trial Monitor’s responsibility to make sure that each patient has given his/her written consent to allow this direct access.

The investigator shall ensure that the documents provided to the Sponsor do not contain the patient’s name or any identifiable data.

[name], Head of the Biostatistics Unit, will oversee the final trial dataset, along with the PI.

### 2.27. Dissemination policy: trial results, authorship

The study findings will be submitted to a peer-reviewed journal for publication and presented at relevant national and international scientific meetings.

The authorship is based on the criteria established by the International Committee of Medical Journal Editors (https://www.icmje.org/recommendations/browse/roles-andresponsibilities/defining-the-role-of-authors-and-contributors.html, accessed on August 1st, 2022).

### 2.28. Plans to give access to the full protocol, participant level-data and statistical code

The protocol is available on EudraCT Number: 2019-004498-18. No public access to the patient dataset is planned to be given at this moment. [name], the Head of the Biostatistics Unit, will oversee the dataset and granting access to this information will be evaluated on a case-by-case basis and upon reasonable request by the interested part.

## 3. Discussion

NPC is a complex orphan disease, consisting of an unmet medical need for patients suffering from it. Although there are over 20 ongoing studies on NPC registered in the ClinicalTrials.gov database, conducting clinical trials for assessing new therapeutic options can be quite challenging, given the disease’s low prevalence. Different therapeutic approaches are under study (e.g., Miglustat, Arimoclomol, N-Acetyl-L-Leucine), but, to the best of our knowledge, this is the first clinical trial studying the effects of EFV in adult- and late-juvenile-onset NPC.

As mentioned before, neuronal cholesterol metabolism is key for LTP, which is a major event for synaptic plasticity. The enzyme CYP46A1 hydroxylates the cholesterol and mediates the main pathway for its degradation in the brain.^[9,10]^ Given that NPC1 binds cholesterol and participates in its intracellular mobilization, we hypothesized that NPC1 would have a synapse-specific role in redistributing cholesterol and mobilizing CYP46A1 to the synaptic membrane required for LTP. We believe that the capacity of EFV to activate the CYP46A1 could compensate for NPC1 deficiency and correct synaptic changes, therefore compensating cognitive and psychiatric alterations in patients with NPC. This hypothesis is supported by preclinical data^[12,14]^ suggesting that low-dose EFV may be a promising alternative for NPC patients.

On the other hand, this study has limitations. First, the already mentioned small sample size due to the disease’s low prevalence. Therefore, interpreting the results may be tough, given that we cannot safely exclude that a given outcome happened by chance. Second, it has a single-arm design (absence of a control group). Although justifiable by the natural history of the disease, the unexpectedness of spontaneous improvement, and the lack of expected placebo effects, this type of design has idiosyncratic limitations since it could be argued that responders would have responded equally if treated only with SoC. Furthermore, the absence of a frame of reference for comparison could also make the results hard to interpret.

This study may provide direct benefit to enrolled patients in terms of slowing down the disease progression. If the preclinical results are reproducible in a clinical setting, NPC patients may have a new therapeutic option in the future to address their currently unmet medical needs. Nonetheless, future Phase III clinical trials would be needed to confirm the findings of this trial.

**Note: This protocol was written following the SPIRIT statement*.^[15]^

### 3.1. Trial status

The current protocol version is 3.1 (March 24th, 2022). This trial is currently on the screening phase (August 2022).

### 3.2. Informed consent materials

Please refer to *Supplementary Material*, http://links.lww.com/MD/I123.

### 3.3. Plans for collection, laboratory evaluation, and storage of biological specimens for genetic or molecular analysis in the current trial and for future use in ancillary studies, if applicable

Biological samples from blood tests and CSF analysis will be analyzed during the conduct of the trial and will be stored in the HUB-ICO-IDIBELL Biobank, which manages and regulates the different biological samples collected at the BUH, Catalan Institute of Oncology (ICO), and other associated centers, under the current Spanish law 14/2007 and the Royal Decree 1716/2011. Additional information on the HUB-ICO-IDIBELL Biobank can be found at https://idibell.cat/en/services/scientific-and-technical-services/biobank/.

Patients will be informed about the biological samples’ storage along with all study procedures by the recruiting investigator. This information will also be displayed in the Patient Information Sheet, and all patients must sign the written informed consent prior to any study-related procedure, including the storage of any biological sample.

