### 2.3. Interventions

The study intervention is EFV. All patients will be treated orally with 25 mg/d of EFV for 52 weeks (1 year), in addition to SoC. Despite this established 25 mg/d dose, successive blood analyses will be performed during the trial, and those patients with no evidence of a blood 24-OH-Cholesterol increase ≥ 1.5 times their baseline levels will have their EFV dose increased up to 200 mg/d.

According to the SmPC, the recommended antiretroviral dose of EFV for adults is 600 mg/d PO, combined with nucleoside reverse transcriptase antiretroviral inhibitor with or without a protease inhibitor. The dose selected for this trial (25 mg/d) is the 1 administered to the pediatric population with 3.5 to <5 kg of weight. Also, as recommended by the SmPC, patients will be advised to take the medication at bedtime.

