#### 2.3.1. Rationale for dose selection.

Preclinical studies using NPC mouse models used an Efavirenz dose 300 times smaller than the 1 used in HIV patients.^[14]^ Although very small, the dose used has been proven to activate CYP46 and efficiently promoted the recycling of cholesterol in the brains of normal mice.^[14]^

However, extrapolating preclinical doses to a clinical setting is challenging. The significant differences in body size, brain size, and the blood-brain barrier must be considered, among other things. Also, administering humans with a dose as low as the 1 administered in mice would risk not having the desired effect.

Notably, 1 clinical trial (NCT03706885, ClinicalTrials.gov) is currently being conducted in patients with Alzheimer’s dementia using oral doses of EFV of 50 and 200 mg/d to activate CYP46 in the brain.

In light of all that, the study team has selected a dose of 25 mg/d of EFV, considering that the desired effect should be observed with this dose – a dose 24 times smaller than the recommended antiretroviral dose for HIV patients (600 mg/d). Given that increases in plasma 24-OH-Cholesterol concentrations (≥1.5 times the pre-EFV baseline values) have been observed in the preclinical studies, we will perform successive blood tests (every 3 months). If no 24-OH-Cholesterol increases ≥ 1.5 times the pre-EFV baseline values are observed, we shall consider increasing the dose to up to 200 mg/d.

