#### 2.7.1. Study procedure.

Study candidates will be screened during visit 1. Those who meet all the inclusion criteria and none of the exclusion criteria will be invited to participate. Both patient and caregiver must sign the written informed consent, a sine qua non condition for enrollment. Seven study visits will be performed for enrolled patients, and all the information detailed in Table 3 will be gathered.

**Table 3 T3:** Participant timeline.

	Visit 1 (baseline visit)	Visit 2	Visit 2.1	Visit 3	Visit 4	Visit 5	Visit 6
	Screening and enrollment	Start of treatment					End of treatment
	−60/−30 d	Day 0 (Wk 0)	Wk 4 ± 3 d after visit 2	Wk 13 ± 1 wk after visit 2	Wk 26 ± 1 wk after visit 2	Wk 39 ± 1 wk after visit 2	Wk 52 ± 2 wks after visit 2
**Inclusion/exclusion criteria**	✓	✓					
**Written informed consent**	✓						
**Demographic data***	✓						
**Vital signs (BP, HR, T, RR) and body weight**	✓	✓	✓	✓	✓	✓	✓
**Physical examination**	✓	✓	✓	✓	✓	✓	✓
**Neurological examination** ‡	✓	✓	✓	✓	✓	✓	✓
**Neuropsychological assessment** §	✓				✓		✓
**General blood tests** ‖	✓			✓	✓	✓	✓
**Biomarkers:** **24-OH-cholesterol**	✓			✓	✓	✓	✓
**Biomarkers:** **Oxysterols** **Lyso-sm-509**	✓				✓		✓
**EKG**	✓			✓	✓	✓	✓
**Medication dispensing**		✓		✓	✓	✓	✓
**Brain MRI**	✓						✓
**Brain ^18^FDG-PET scan**	✓				✓		✓
**Oculography**	✓				✓		✓
**Abdominal ultrasound**	✓				✓		✓
**Lumbar puncture**		✓†					✓†
**AE recording**	✓	✓	✓	✓	✓	✓	✓
**Concomitant medication recording**	✓	✓	✓	✓	✓	✓	✓
**Patient’s journal**		✓		✓	✓	✓	✓
**Pregnancy test**	✓	✓		✓	✓	✓	✓

AE = adverse event, BP = blood pressure, EKG = electrocardiogram, HR = heart rate, MRI = magnetic resonance imaging, RR = respiratory rate, T = temperature.

(1) Includes genetic diagnosis.

‡ Includes Ataxia Scale (SARA), Dysphagia Scale (EAT-10), Pineda Disability Scale.

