§ CDR-SoB: Clinical Dementia Rating-Sum of Boxes Scale; a-BT: Abbreviated Barcelona Test; WAIS-III/WAIS-IV: Weschler Adult Intelligence Scale, Cubes, Symbol Search, and Vocabulary subtests; FCSRT: Free and Cued Selective Reminding Test; Verbal Fluency Score: Semantic and phonemic tasks (category fluency [CF] and letter fluency [LF]); TMT: Trail Making Test A and B; SCWD: Stroop Color and Word Test; BNT: Boston Test, subtests Naming and Semantic Knowledge Test; JLO: Judgement of Line Orientation Test; DEX: Dysexecution Questionnaire; NPI: Neuropsychiatric Inventory; AES: Apathy Evaluation Scale; BDI: Beck Depression Scale; C-SSRS: Columbia Suicide Severity Risk Scale.

‖ Complete blood count, coagulation tests, and Biochemistry (sodium, potassium, calcium, protein, glucose, urea, creatinine, aspartate aminotransferase, alanine aminotransferase, cholesterol, TSH, T4).

† **Lumbar puncture** will be performed to determine CSF biomarkers (i.e., Beta-amyloid, Tau, and phosphorylated Tau) in those patients who agree to undergo this procedure. The investigator must inform patients and caregivers that this procedure is optional and about the risks involved. Patients who accept it will be required to sign a separate and specific written informed consent (both patients and caregivers must sign it).

We estimate it will take approximately 3 months to complete the enrollment procedure. We expect to carry out the study between 2022 and 2024.

By the moment of submitting this manuscript, participant recruitment (patients’ screening visit) was still in progress.

Participant Timeline

The EFV will be provided by the study sponsor and will be acquired through the Pharmacy Department at BUH. The supplied EFV is to be used exclusively in this clinical trial. The Pharmacy Department will have an updated record of the EFV and manage an inventory that will collect all product entries, dispensing, returns, and disposals.

The records will comply with current regulations and guidelines. Once they are completed, they must be signed and dated by the person in charge. The clinical trial pharmacist will be responsible for maintaining all records of the medication used. The EFV does not require any special storage conditions according to the SmPC and should not be used after the expiry date indicated on the label.

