### 2.8. Sample size

We have not performed a formal sample size calculation. Adult NPC is an orphan disease, with an estimated prevalence of 27 patients in Spain in 2019. The principal investigator (PI) currently follows 14 of these patients at the BUH. Therefore, we expect to enroll a total of 14 patients.

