### 2.10. Assignment of interventions

#### 2.10.1. Allocation: Sequence generation, concealment mechanism, implementation, and blinding (Masking).

Not applicable. This is a single-arm clinical trial; thus, all enrolled patients will receive the study treatment.

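### If biomarker samples are assayed as they arrive, a persistent, uncorrected assay shift between the baseline and week-52 periods cannot be told apart from time on efavirenz in this single-arm trial

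*Protocol article*

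**What the plan says.** On assay timing, section 3.3 of the protocol article states: "Biological samples from blood tests and CSF analysis will be analyzed during the conduct of the trial and will be stored" in the hospital's biobank. It gives no schedule of assay runs.

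For 24-OH-cholesterol the timing is clear. Section 2.3 says that "successive blood analyses will be performed during the trial", section 2.3.1 sets them every 3 months, and Table 3 places them at Visits 1, 3, 4, 5 and 6. Each result is compared with the patient's own baseline while the trial runs. Table 3 places oxysterols and lyso-SM-509 at Visits 1, 4 and 6, and the optional lumbar puncture at Visits 2 and 6.

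On design, section 2.10.1 says "This is a single-arm clinical trial; thus, all enrolled patients will receive the study treatment". Section 2.8 says "We have not performed a formal sample size calculation" and "Therefore, we expect to enroll a total of 14 patients". Section 2.7.1 says "We estimate it will take approximately 3 months to complete the enrollment procedure". Visit 1 falls 30 to 60 days before Visit 2, and Visit 6 at "Wk 52 ± 2 wks after visit 2".

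Tables 1 and 2 list these markers as secondary biological outcomes, with change as the objective. Section 2.14 calls them exploratory and analyses them with the technique used for the primary outcome. It names no term for assay run or calendar period.

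**The concern.** A within-patient change is trustworthy only if both ends are measured on the same scale. Where enrolment is long, early and late assay runs each contain a mix of baseline and follow-up samples, and a control arm lets a common shift be subtracted. This trial has neither protection. If samples are assayed as they arrive, the baselines are measured in one calendar period and the week-52 samples in a later one. A lasting difference between the two periods then enters the mean change in full. A larger sample would not dilute it, the confidence interval would not reflect it, and no model fitted to these data could estimate it.

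At stake is how the biochemical results are read. The trial's hypothesis is activation of CYP46A1, and 24-OH-cholesterol is the document's own marker of response to efavirenz. With 14 patients and no comparator, readers are likely to lean on these markers, although they are exploratory. An assay artefact could create a change or cancel a real one.

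**Working it through.** The plan gives no figure of its own to reproduce: it has no power calculation, and it states no assay precision.

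**Step 1. Do baseline and week-52 samples overlap in calendar time?** Inputs: Visit 1 at 30 to 60 days before Visit 2; Visit 6 at 52 ± 2 weeks after Visit 2; Visit 1 dates spread over 13 weeks (the estimated 3 months).

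- Visit 1 to Visit 6 within a patient: from 50 × 7 + 30 = 380 days (54.3 weeks) to 54 × 7 + 60 = 438 days (62.6 weeks).
- Earliest Visit 6, counted from the first Visit 1: 30/7 + 50 = 54.3 weeks. The last Visit 1 is at week 13, so the blood gap is at least 54.3 − 13 = 41.3 weeks.
- CSF baseline is at Visit 2. The latest Visit 2 is at 13 + 60/7 = 21.6 weeks, so the CSF gap is at least 54.3 − 21.6 = 32.7 weeks.

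There is no overlap. Simulating the blood-biomarker schedule with 13 weeks of uniform enrolment gives a correlation of about 0.98 between calendar time and time on study. With 26 weeks of enrolment it is 0.94 and with 52 weeks 0.82, so somewhat slower recruitment would not remove the problem.

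**Step 2. What does a shift do to the inference?** Assumptions, none of them in the document: no true change; a two-sided 95% paired t-interval on log-change; a common multiplicative shift *s* between the periods; SD of log-change 0.2, 0.3 or 0.4. The interval excludes zero with the probability that a non-central t variable with n − 1 degrees of freedom and non-centrality ln(1 + s)/(SD/√n) falls outside ± the critical value. For n = 14 the critical value is 2.160. Example: s = 10% and SD = 0.2 give ln(1.10)/(0.2/√14) = 1.78, and a probability of 38%.

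| Shift | SD 0.2 | SD 0.3 | SD 0.4 |
|---|---|---|---|
| 2% | 6% | 6% | 5% |
| 3% | 8% | 6% | 6% |
| 5% | 14% | 9% | 7% |
| 10% | 38% | 20% | 13% |
| 15% | 68% | 37% | 23% |
| 20% | 88% | 56% | 35% |

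**Step 3. CSF.** Lumbar puncture is optional and is not offered to patients on anticoagulants, so 14 is an upper limit. With an assumed 7 patients, SD 0.3 and a 10% shift, the non-centrality is ln(1.10)/(0.3/√7) = 0.84, and the probability is 11%.

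**Step 4. After the fix.** If all of a patient's samples are in the same run, a shift common to that run cancels in the difference. The probability returns to the nominal 5%, provided that storage does not itself change the analyte.

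**The case against.** A reader might infer that the plan has every marker assayed visit by visit, and that any assay shift will therefore be read as a drug effect. The document does not support that. Section 3.3 is one general sentence about specimens. Running assays are documented for 24-OH-cholesterol only. For the other markers, a batch run after the last Visit 6 but before the trial closes would also fit the sentence, and nothing requires their results earlier. Nor is any shift enough. If the baselines span several runs, ordinary run-to-run variation goes into the SD and the interval allows for it. Only a lasting difference between the periods that calibration leaves uncorrected is confounded. A laboratory manual may provide bridging controls that reduce it.

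Other limits also stand. The shifts and SDs are assumed. The paired t-interval stands in for the planned ANCOVA, generalized or non-parametric analysis. A shift of 5 to 20% would not on average mimic the 1.5-fold rise that the plan itself looks for in 24-OH-cholesterol. The discussion already concedes the lack of a comparator.

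These objections narrow the point but do not remove it. The article makes a positive statement about assay timing, so this is not just a detail left to another document. The conceded limitation is the missing control group. Assay shift is different, because it can be removed without one.

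**Conclusion.** The point holds in conditional form: if samples are assayed as they arrive, a persistent and uncorrected assay shift is inseparable from time on efavirenz. The condition is documented for 24-OH-cholesterol and is left open by the wording for oxysterols, lyso-SM-509 and the CSF markers. The size depends on the assumed shift and SD: negligible at 2 to 3%, noticeable at 5%, and serious at 10% or more when the SD is small. The lack of overlap rests on enrolment taking about as long as estimated. The primary cognitive outcome is untouched. This is an avoidable weakness in exploratory outcomes, worth correcting because the correction is cheap; it is not evidence that any result will be wrong.

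**What to change.** Amend section 3.3 and the laboratory instructions as follows.

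- **Oxysterols, lyso-SM-509, CSF beta-amyloid, tau and phosphorylated tau:** store the aliquots in the biobank already planned. After the last Visit 6, assay all of a patient's visits in the same run, with laboratory staff masked to visit.
- **24-OH-cholesterol:** keep the real-time results for the monitoring already planned. Take the 52-week outcome estimate from one end-of-study run of stored aliquots from the same patients.

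Cost: the first group needs no extra assays, only deferred ones. For 24-OH-cholesterol there are up to 14 × 5 = 70 repeats if all five visits are re-assayed. Results come later. Baseline aliquots are stored about a year longer than week-52 aliquots, which ties storage time to visit, so the stability of each analyte over that period must be confirmed first.

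The change does not separate an efavirenz effect from the natural course of the disease, and it does not alter any dose rule.
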